## **Survey Delivery**

The logistics and timing of MPS delivery will be similar for all *microtrials* with exceptions pointed out in each of the microtrials below. A brief description of the MPS delivery schema follows.

To help improve survey response and completion rates, an *SMS* *notification* will be sent to those who have been randomly selected to participate in the mobile phone survey. Previous studies have shown that notification SMS improve survey response and cooperation rates and decreases refusal rates.^11^ This SMS is meant to notify the potential respondent of the upcoming survey and will describe the purpose of survey, expected time commitment, and the survey’s sponsoring agency. The exact wording of the SMS and the timing of SMS delivery will be guided by focus group discussions (FGD) from a previous protocol (JHU IRB No: 0000709). Respondents will not be required to reply to the SMS in order to participate in the IVR survey; with the exception of *microtrial #2* (details can be found in the description of *microtrial#2)*.

The notification SMS will be sent before and on the same day on which the MPS will be sent. As discussed above, the exact timing of the notification SMS will be guided by the focus group discussions. Due to possible country specific mobile network problems, at a minimum, the SMS will be sent at least one hour before the MPS is sent; therefore ensuring the SMS reaches the participant before the IVR survey is sent. After the notification SMS is sent, the MPS will be sent to the same randomly generated mobile phone number. When a randomly dialed number is connected (i.e. a respondent picks up the phone), the respondent will be presented with a brief pre-recorded introduction to the study and provided an opportunity to select the survey’s language (except for *microtrial #5;* details provided below*)*. An example of the narrated introduction and language selection is, “Hello, its [Name] from the [Implementing Agency]. Earlier today, we sent you a text message about participating in a mobile phone survey.” After hearing the introduction, participants will be asked to select their preferred language for which the IVR survey will be narrated, “Please pick a language to continue hearing the survey instructions [and how you could qualify for free airtime (if countries are using airtime incentive] Press 1 to continue in [Language X] Press 2 to continue in [Language Y]” The results of the FGD (JHU IRB No: 0000709) will assist in the selection of the exact wording for the introduction and language selection.

After the language selection, the speaker will provide a more detailed description of the study which includes the purpose, duration, risks, benefits, and the sponsoring agency. If incentives are not prohibited in the country, participants will also be told about requirements to receive an incentive and the incentive amount. Potential respondents will be asked a demographic screening question. Respondents will be screened on age; those who indicate being less than 18 years old will be thanked for their interest and the survey will be terminated. If screening criteria are met, respondents will then be asked whether they agree to participate in the study (consent). Respondents who choose to continue with the survey - after hearing about its purpose, procedures and voluntary nature - will be asked to press a number on their keypad to indicate their willingness to continue (e.g. “Press 1 if you would like to participate in this survey. Press 3 if you do not want to participate in the survey”). Participants will be asked again to confirm their participation (e.g. “You have indicated that you do wish to complete the survey, press 1 to continue the survey or press 3 to end this survey”) to ensure that consent (or refusal) was not mistakenly provided. Respondents who do not agree to participate, will be thanked for their time and the survey will end. Following consent, respondents will receive and answer a series of NCD modules whose order of presentation is randomized as described above.

At any time after the MPS has been initiated (i.e. participants met screening criteria, consented, and began answering NCD topical questions) participants will be able to formally opt-out of survey participation by pressing a sequence of buttons on their mobile phone (The precise combination of buttons will be determined by in-country programming and implementation teams). NCD surveys will only be sent to participants once; that is participants who were ineligible due to screening criteria, refused consent, or formally opted out during the survey will not have an additional NCD survey sent.

The MPS will be delivered at random times ranging from 8:00am to 8:00pm local time. The exact time window to deliver the notification SMS and MPS will be determined by each country during the FGD (JHU IRB No: 0000709).

The potential survey outcomes are depicted in figure 3. In a large proportion of the randomly selected mobile phone numbers, the randomly dialed mobile phone number may not exist, participants may refuse to participate in the MPS, or the mobile phone number may be valid, but the IVR survey was not initiated. Reasons for this latter category include, (1) phone was turned off or out of battery, (2) mobile phone was out of network coverage area, and (3) personal reasons, which include not hearing the mobile phone ring or respondent hanging up before consenting to the study. In these instances where the MPS was not initiated by a respondent, no future call back attempts to enroll participant will be made. Moreover, for respondents who initiate the IVR survey, but do not complete it (labeled an ‘incomplete survey’ in the figure), no call back attempts to re-initiate the survey will be made. Note, that as described in the sample size section, a sub-sample of participants (n=30) will be called back by a human interviewer to ask why they did not complete the survey. Unlike traditional household surveys, multiple attempts to achieve participant response are not needed since the selection of mobile phone numbers and timing of delivery are both random, thereby reducing the potential for non-response bias, but also because of the very large pool of possible respondents in the sampling set of all mobile phone owners.

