Once a respondent is contacted or participates in one of the proposed microtrial, they will be ineligible for participation in future microtrials. In each *microtrial*, there will be a single random selection of mobile phone numbers without replacement. However, since some participants own multiple mobile phones and phone numbers, it is possible that some participants may be randomly selected to participate in more than one microtrial.

*2.* ***Address any privacy issues associated with recruitment. If recruitment itself may put potential participants at risk (if study topic is sensitive, or study population may be stigmatized), explain how you will minimize these risks.***

Privacy issues associated with recruitment are anticipated to be minimal and similar to those associated with other face-to-face, phone or internet-based surveys. Participants will be sent an SMS alerting them of an upcoming survey and will then receive a phone call asking their willingness to respond to survey questions using their personal mobile phones. The incoming phone number will be the same for the text message and the phone call. Anyone not willing to complete the survey may choose to: 1) not answer the phone, 2) hang up any time after answering the phone, or 3) indicate their desire not to complete the survey by pressing a specified digit. Other individuals associated with or in proximity of respondents are unlikely to know that respondents are being recruited for the study unless the responded chooses to make this known.

B. Consent Process:

1. ***Describe the following details about obtaining informed consent from study participants. If a screening process precedes study enrollment, also describe the consent for screening.***

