IVR surveys will be pushed out by the system until 100 respondents have completed the survey. Overall contact, response, and completion rates will be calculated and applied to sample size calculations for the *microtrials*. The average time spent per question, in both completed and incomplete surveys, as well as average time spent to complete the survey will be tabulated. We anticipate that there will be a low completion percentage (i.e. all survey questions were answered) as participants may not want to spend a long time answering an IVR survey. We will assess the time point where between 40-60% of the participants terminate/drop-off from the IVR survey. For example, 50% of participants that initiate the IVR survey may stop the survey after answering questions for 10 minutes. For the subsequent *microtrials*, we will remove questions and NCD modules (i.e. shorten the questionnaire) until the average time spent is equal to the amount of time where 40-60% of participants drop-off from the survey. Technical glitches in survey delivery, incentive delivery, and sensitizing short message service (SMS) will also be assessed and resolved prior to commencement of the *microtrials.*

*Microtrial #1*- Evaluation of incentive amount

This *microtrial* seeks to examine whether there is a differential effect in completion rates based on incentive amount. This trial will be the first *microtrial* conducted. Participants will be randomized to receive one of three incentive amounts, in the form of airtime, which will be sent to participants upon completion of the IVR survey. The study arms are: 1) no incentive, 2) X USD incentive transferred after survey completion, where X is commiserate with the expected time commitment, daily wage, and its exact amount will be guided by FGDs and in consultation with country-partners, and 3) 2X incentive transferred after survey completion; where 2X is twice the amount of incentive in arm 2.

The response and completion rates will be examined by study arm to inform the incentive amount for *microtrial* #2. If there is an appreciable difference in response and completion rates between two incentive groups, the incentive amount that yields the highest response and completion rates will be used for *microtrial* #2. If there is no difference in response and completion percentages by incentive amount, the lower incentive (X) will be used for *microtrial* #2.

*Microtrial #2*- Evaluation of incentive timing

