In microtrial #7, participants will be asked to answer two surveys (IVR and call center [CATI]) composed of the same questions so that question validity can be assessed. For example, analyses will be conducted to observe whether some people may be more likely to report unhealthy habits when taking the automated IVR survey as compared to a call center because the human element is removed in an IVR survey.

Risk factor data will be collected and stored from other microtrials. This data will be compared to publically available results and national estimates to help determine if the protocol’s mobile-collected risk factor’s prevalence are similar to national estimates of household collected data. This will help answer whether the protocol’s mobile phone sample is as healthy, or unhealthy, as the traditionally administered surveys.

*5.*  ***Describe whether you are collecting or storing personal identifiers, and if yes, why you need them, and when and how you plan to dispose of them. Signatures on consent forms are considered to be identifiers.***

We will not collect personal identifiers via the consent process. Mobile phone numbers that were randomly generated are the personal identifiers. Because of the nature of the trial, the mobile phone numbers are needed to generate data. While phone numbers will initially be logged in the VOTOmobile platform alongside the data collected, immediately after each microtrial has been completed, the PI will download the database from the VOTOmobile platform and permanently delete the column containing mobile phone numbers. Phone numbers need not be retained for purposes of the study. No other potentially individually identifying data will be collected.

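### Random number selection and a large pool do not reduce non-response bias, so the mobile-versus-national prevalence comparison describes single-attempt responders only

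*Protocol*

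**What the plan says.** The protocol's Survey Delivery section (V.C.1) allows one survey call per selected number. Where the survey is not initiated, "no future call back attempts to enroll participant will be made". It gives two reasons. First, "multiple attempts to achieve participant response are not needed since the selection of mobile phone numbers and timing of delivery are both random", and the sentence goes on: "thereby reducing the potential for non-response bias, but also because of the very large pool of possible respondents". So the reduction in bias is credited to random selection and random timing, and the size of the pool is a second, separate reason. The sentence also sets this approach apart from traditional household surveys.

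The same paragraph lists why a valid number may not start the survey: the phone is off or has no battery, the "mobile phone was out of network coverage area, and (3) personal reasons, which include not hearing the mobile phone ring", or the person hangs up before consenting. On timing, "The MPS will be delivered at random times ranging from 8:00am to 8:00pm local time".

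The data analysis section (V.C.4) then compares risk-factor data from microtrials other than #7 with published national estimates from household surveys. Its stated purpose: "This will help answer whether the protocol’s mobile phone sample is as healthy, or unhealthy, as the traditionally administered surveys".

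The sample size section (III.B) and the follow-up paragraph at the end of Microtrial Designs plan human call-backs, with up to three tries, to 30 non-responders, 30 refusers and 30 non-completers per microtrial. They collect reasons and demographics, and the demographics are set against those of completers.

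**The concern.** The claim gives the design a property that it does not have. Random generation of numbers makes the dialled sample random. Non-response bias arises afterwards, among those dialled, if the people who answer and stay on the line differ in risk-factor prevalence from those who do not. Several of the protocol's own reasons for non-initiation depend on the person or the place and can plausibly be related to age, work, rural residence or lifestyle.

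What is at stake is the reading of the national comparison. Validity of mobile surveys is an aim of the wider programme, and this comparison is the protocol's check on whether the mobile sample resembles traditionally surveyed populations. The contrast with household surveys implies that those make repeat attempts, so a difference in contact effort is built into the comparison. A reader who accepts the claim would attribute a gap to phone ownership or survey mode, or take agreement as support for validity, although part of either result may come from single-attempt non-response.

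**Working it through.** The protocol attaches no figure to this claim, so there is nothing of its own to reproduce. The check asks what the bias depends on.

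**Formula.** For a prevalence estimated in responders,

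bias = (1 − response proportion) × (prevalence in responders − prevalence in non-responders).

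There is no term for the number of people dialled, the number who complete, or the size of the pool.

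**Inputs.** The protocol gives neither a response proportion for this purpose nor any difference by risk status, so both are assumptions. The protocol's 30% completion percentage has another denominator (people who consented, in the sample size section) and is not this response proportion. The protocol's response rate also leaves out numbers of unknown status, which include people who did not pick up.

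| Assumed response | 5-point difference | 10-point difference |
| --- | --- | --- |
| 10% | 0.9 × 5 = 4.5 points | 0.9 × 10 = 9.0 points |
| 30% | 0.7 × 5 = 3.5 points | 0.7 × 10 = 7.0 points |
| 50% | 0.5 × 5 = 2.5 points | 0.5 × 10 = 5.0 points |

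With no difference between responders and non-responders the bias is zero at any response.

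**More dialling against more attempts.** Assume a true prevalence of 30% and single-attempt response of 20% in people with the risk factor and 30% in people without it.

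- One attempt: 0.3 × 0.2 / (0.3 × 0.2 + 0.7 × 0.3) = 0.06 / 0.27 = 22.2%, a bias of −7.8 points.
- One attempt, dialling on to a larger number of completes (simulated): 23.1% at 376, 22.2% at 6,926, 22.3% at 100,000. The estimate settles on the biased value.
- Repeat attempts to the same people, each with an independent chance of response: 23.2% after two, 24.2% after three, 25.7% after five. The bias shrinks because more of the selected people respond.

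The direction depends on the assumption: response of 40% against 30% gives 36.4% after one attempt, and equal response gives 30.0%.

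**Random timing.** A randomly timed call gives each person a chance of being reached that reflects their availability over the whole calling window. That is better than one fixed hour, when some people would always be missed. People who are seldom available still have a low chance on a single call, and random timing does not change that.

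**Precision beside bias.** The national comparison concerns the microtrials other than #7. From Table 1, 6,926 − 810 = 6,116 completers per country, baseline included. If all were pooled, the 95% half-width at a prevalence of 30% would be 1.96 × √(0.3 × 0.7 / 6,116) = 1.1 points. An assumed bias of 3.5 points is about three times that, and the interval would not reveal it.

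**What the call-backs can show.** With 30 people per group, the 95% half-width for a proportion is 1.96 × √(0.3 × 0.7 / 30) = 16.4 points at 0.3 and 17.9 points at 0.5, before allowing for people who are not reached. The call-backs are not stated to collect risk factors, so they cannot supply the responder/non-responder difference in the formula.

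**The case against.** The strongest defence is that the protocol claims only a reduced potential for bias and that random timing does some good. It also plans call-backs to non-responders with a demographic comparison, so its authors did not regard non-response as ignorable. All of this stands. It does not rescue the statement that random selection makes repeat attempts unnecessary, nor the argument from pool size.

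Four stronger readings are tempting, and the document does not support them.

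- A reader might infer that the national comparison treats the mobile sample as unselected. It does not: the comparison is posed as a check on whether the sample resembles the population in traditional surveys.
- A reader might infer that the protocol sets out a scheme of replacing non-responders with fresh numbers. It does not say so. The recruitment section states that "there will be a single random selection of mobile phone numbers without replacement", and dialling to a target is stated only for the baseline survey: "IVR surveys will be pushed out by the system until 100 respondents have completed the survey". Continued dialling in the microtrials is a fair inference from the pool argument, no more.
- A reader might count the lack of weighting or standardisation as an omission. The analysis section is brief by design, and an analysis plan that is not at hand may contain it. The section does not say that the comparison will be crude.
- A reader might extend the problem to the randomised comparisons. Contact, response and completion are the outcomes there, and non-response is part of what is measured, so those comparisons stand.

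It is also fair to say that the national comparison is descriptive and is not one of the four primary objectives.

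**Conclusion.** The rationale for the single attempt is wrong as written. Random selection of numbers and a large pool do not reduce non-response bias, and random timing reduces it only in the limited sense of avoiding one fixed hour. A gap or an agreement between mobile and national prevalence will mix single-attempt non-response with phone coverage and mode effects, and the planned call-backs are too small and too narrow in content to separate them.

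The size cannot be derived from the document. Under the assumptions above (response of 10% to 50%, a difference of 5 to 10 points) it runs from 2.5 to 9.0 points, with 3.5 points at 30% response and a 5-point difference. It is zero if responders and non-responders have the same prevalence. The correction limits what the national comparison can conclude and leaves the randomised results as they are.

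**What to change.** 1. In Survey Delivery, withdraw the statement that random selection, random timing or pool size makes repeat attempts unnecessary by reducing non-response bias. Present the single attempt as an operational choice and name non-response bias as a limitation. It can still be said that random timing avoids always missing people who are unavailable at one hour.
2. In the data analysis section, state that the comparison with national estimates is descriptive of single-attempt responders, that any gap or agreement combines non-response, phone coverage and mode, and that it is read beside the call-back demographics. Note that those rest on 30 people per group and are not stated to include risk factors.
3. As a low-cost addition, show the mobile prevalence both crude and standardised to the national adult distribution of the demographics collected. Objectives 1 to 3 already rely on such variables; which ones are usable depends on the questionnaire.

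The first two changes are wording and need no extra calls. The third is one analysis step on data already planned. Its intervals will be somewhat wider, and it does not remove non-response bias within demographic groups.

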**Figure 3. IVR Survey Delivery Schedule and Possible Outcomes**

**
[figure not shown]
**

***** Timing of Notification SMS and window of survey delivery to be determined by FGD

**Microtrial Designs**

A description of each of the seven *microtrials* and the baseline IVR survey follows. Differences between the *microtrial* design and the IVR questionnaire and delivery (sections detailed above) will be pointed out. A broad description of the *microtrials* can be found in Table 2. Where participants have the opportunity to earn an airtime incentive, participants will be told of the requirements to earn this incentive during the survey’s introduction.

Objective 1: Evaluation of Incentives

*Baseline IVR* Survey

The purpose of the baseline IVR survey is to assess baseline completion rates to inform sample size calculations for the seven *microtrials*, to finalize the questionnaire used in IVR delivery, and to ensure that the IVR platform is functioning well (i.e. delivering SMS notifications, IVR surveys, and incentives correctly and as indicated in the protocol). For the baseline IVR survey, a 30 question containing survey will be sent to randomly dialed participants at random times of the day (See Appendix 1 for the questionnaire to be used). An airtime-based incentive of approximately $1.00 USD will be transferred to a respondent’s mobile phone if the survey is completed (i.e. all questions answered). The exact amount of airtime incentive will be guided by the finding of the formative FGD (JHU IRB No: 0000709)

IVR surveys will be pushed out by the system until 100 respondents have completed the survey. Overall contact, response, and completion rates will be calculated and applied to sample size calculations for the *microtrials*. The average time spent per question, in both completed and incomplete surveys, as well as average time spent to complete the survey will be tabulated. We anticipate that there will be a low completion percentage (i.e. all survey questions were answered) as participants may not want to spend a long time answering an IVR survey. We will assess the time point where between 40-60% of the participants terminate/drop-off from the IVR survey. For example, 50% of participants that initiate the IVR survey may stop the survey after answering questions for 10 minutes. For the subsequent *microtrials*, we will remove questions and NCD modules (i.e. shorten the questionnaire) until the average time spent is equal to the amount of time where 40-60% of participants drop-off from the survey. Technical glitches in survey delivery, incentive delivery, and sensitizing short message service (SMS) will also be assessed and resolved prior to commencement of the *microtrials.*

*Microtrial #1*- Evaluation of incentive amount

This *microtrial* seeks to examine whether there is a differential effect in completion rates based on incentive amount. This trial will be the first *microtrial* conducted. Participants will be randomized to receive one of three incentive amounts, in the form of airtime, which will be sent to participants upon completion of the IVR survey. The study arms are: 1) no incentive, 2) X USD incentive transferred after survey completion, where X is commiserate with the expected time commitment, daily wage, and its exact amount will be guided by FGDs and in consultation with country-partners, and 3) 2X incentive transferred after survey completion; where 2X is twice the amount of incentive in arm 2.

The response and completion rates will be examined by study arm to inform the incentive amount for *microtrial* #2. If there is an appreciable difference in response and completion rates between two incentive groups, the incentive amount that yields the highest response and completion rates will be used for *microtrial* #2. If there is no difference in response and completion percentages by incentive amount, the lower incentive (X) will be used for *microtrial* #2.

*Microtrial #2*- Evaluation of incentive timing

This microtrial seeks to examine whether the timing of incentive delivery (either given before the survey or afterwards) has an effect on contact, response, and/or completion rates. Participants will be randomized to one of three study arms: 1) no incentive, 2) a pre-paid airtime incentive; where 20-40%% of the total incentive (X) is sent to the respondent’s mobile phone after the sensitizing SMS and prior to initiation of the survey, and with the remaining 60-80% being sent after the survey’s completion (i.e. all questions answered), or 3) a promised incentive where 100% of the incentive amount is sent to the respondent’s mobile phone after the IVR survey is completed. With existing technology, the minimal amount of airtime that can be transferred is 1 USDThe total incentive amount (X) in this microtrial will be the incentive amount from *microtrial* #1 that produced the highest response and completion rates.

*Microtrial #3*- Evaluation of incentive structure

This microtrial seeks to examine whether the incentive structure (a fixed incentive amount or a lottery-based incentive) has an effect on response and completion rates. Respondents will be randomized to one of three study arms: 1) no incentive, 2) a fixed airtime incentive delivered after survey completion where the amount of the incentive is determined by *microtrial* 1, and 3) a lottery airtime incentive of an amount five times greater than the amount in the second study arm; where the odds of winning the lottery are 1:20.

Objective 2: Evaluation of the Surveys Introduction

*Microtrial #4*- Evaluation of content and voice of IVR survey’s introduction

This microtrial seeks to examine whether the content of the IVR survey’s introduction (motivational vs informational) and the survey’s narrative voice (male vs female) has an effect on contact, response, and/or completion rates. Participants will be randomized to one of four study arms with varying survey introduction content and voices: 1) male voice, informational content, 2) male voice, motivational content, 3) female voice, informational content, and 4) female voice, motivational content. Participants in each study arm will receive the same incentive.

*Microtrial #5*- Evaluation of a human operator IVR survey introduction

This microtrial seeks to examine whether the survey introduction’s modality (human operator versus those who receive an IVR survey introduction) has an effect on survey response and completion rates. Participants will be randomized to one of two arms: 1) a human will call the RDD-generated mobile phone number and read the survey’s introduction. The operator will answer any questions the participant may have, consent the participant and then patch the participant into the IVR survey, and 2) the participant will receive a IVR survey with a survey introduction in IVR format and similar to the previous *microtrials*.

Objective 3: Evaluation of the Sampling Frame

*Microtrial #6*- Evaluation of the sampling frame of mobile phone numbers

This microtrial seeks to examine whether the source of the mobile phone numbers has a differential effect on the IVR survey’s response and completion rates. The previous five *microtrials* relied on a RDD sampling frame. In this microtrial, we will obtain a de-identified list of mobile phone numbers from either a mobile network operator or from a previously conducted household survey where participants had consented to be contacted for additional studies. Participants will be sent an IVR survey with the top performing survey introduction (results from microtrials 4 and 5) and the top performing incentive (microtrials 1-3).

Objective 4: Evaluation of Survey Modality

*Microtrial #7*- Evaluation of CATI and IVR survey metrics

This microtrial seeks to examine whether the survey’s modality (IVR versus CATI) has a differential effect on the survey’s response and completion rates and to assess the ‘inter-modal reliability’. Participants will be randomized to one of two arms: 1) IVR then CATI or 2) CATI then IVR. Participants in the first study arm will receive an IVR survey first, followed by a CATI survey 7 days later. Participants in the second study arm will receive a CATI survey first followed by an IVR survey 7 days later. At initial enrollment, participants will be clearly explained that they are being enrolled in a microtrial where they will be contacted twice. The questionnaires used in both study arms will the same. This crossover design will allow for an assessment of response consistency, adjusted for the risk of ‘priming’ after exposure to the prior modality. This is the only *microtrial* that has participants answer two NCD surveys. The amount/timing/structure of incentive will be guided by the first three *microtrials*; where the incentive that yielded the highest response and completion rates will be provided to all participants in *microtrial* #7.

Follow-up of Non-response, Refusals, and Incomplete Interviews

For participants who were selected for the seven *microtrials,* a random sub-sample of participants who did not initiate the IVR survey, refused to participate, or partially completed an IVR survey, will be called back by a human operator using the same telephone number that was associated with the IVR. The study team will attempt to reach individuals up to three times. Unreached follow-ups will be documented. If successfully reached, the team will consent and interview participants to explore reasons for participant’s non-response, refusal, or incomplete surveys using a semi-structured guide (See Appendix 2). Demographic information from non-responders, refusals, and incomplete surveys will also be collected and examined in relation to the distribution of those who fully complete the survey.

**Table 2.** Study designs for Microtrials

|  | **Microtrial#1**  **Incentive Amount** | **Microtrial#2**  **Incentive Timing** | **Microtrial#3**  **Incentive Structure** | **Microtrial#4**  **IVR Intro features** | **Microtrial#5**  **IVR vs Human Intro** | **Microtrial#6**  **Sampling frame** | **Microtrial#7**  **Survey Modality** |
| --- | --- | --- | --- | --- | --- | --- | --- |
